## Methods

### Design

The study is designed as a prospective follow up study. The patients will complete the questionnaires, once preoperatively in the outpatient department and three times postoperatively; before discharge and 12 and 52 weeks after the operation. The inclusion period will be one year beginning in October 2010. The study includes a reliability test of CMD-SQ regarding this specific population, and investigated by means of a Kappa.

The reliability of CMD-SQ is tested by including 40 patients who will answer the CMD-SQ two times. The aim is to investigate whether the questionnaire responses will change over time regarding this specific population (test-retest). The hip patients will be asked to fill in the CMD-SQ at first in the outpatient department, when they join the Joint Care School, and next when they arrive to the inpatient department just before their operation. The main issue is that no essential changes had happened to the patients between the two measurements.

After the test-retest of the CMD-SQ, patients will be included for the next part of the study. When the hip patients arrive to the Joint Care School, they are asked to fill in the questionnaires: CMD-SQ, EQ–5D, SF–12, RCS and OHS. The shoulder patients are asked to fill in the questionnaires: CMD-SQ, EQ-5D, SF-12 and OSS when they arrive to the outpatient department for the first time. Both groups – hip and shoulder patients will be asked to fill in the questionnaire HVOK just before their discharge from the inpatient department. The patients are asked to fill in the questionnaires: CMD-SQ, EQ-5D, SF-12, RCS, HVOK and OHS/OSS 12 and 52 weeks after the operation. Postoperatively, the questionnaires are sent to the patients by mail and the patients are asked to return the questionnaire in the enclosed stamped and addressed envelope. If the patients do not return the questionnaire in 14 days, a new questionnaire is mailed. If the second questionnaire is not returned the patients are called and asked to return the questionnaire, or asked why they do not want to fill in the questionnaire. These precautions are taken in order to increase the response rate.

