### Statistical analysis

The test-retest reliability is analyzed by means of an Kappa and a value above 0.70 is recommended in a clinical study
[42].

The data from the preoperative questionnaire, the postoperative questionnaire just before discharge from the inpatient ward, and the questionnaire data from 12 and 52 weeks after the operation, will be analysed using a multiple linear regression test in order to investigate whether there is a correlation between patients´ anxiety and concern, and their perceived quality and outcome of treatment. It is assumed that the data are normally distributed and the will be made to different Multiple Linear Regression analysis where the first will be between baseline and after 12 weeks and the second between baseline and 52 weeks.

The results of the CMD-SQ before the operation and 3 and 12 months postoperatively, are considered the primary outcome, whereas the results of SF-12, EQ-5D, OHS/OSS, RCS and HVOK are the secondary outcome. The main result is a correlation between the primary outcome and the secondary outcomes. The analysis will be done separately and without mutual influence.

Data will be tested for confounder using the Charlson Index and social demographic data (i.e.: gender, age, weight, height, citizenship, civil status and educational level).

Missing data will be labelled as missing in all the questionnaires. For the comparative analysis for the dropouts and the respondents the categorical variables as gender, citizenship, civil status, Charlson Index and educational level will be analyzed using a chi^2 test. For the continuous variables age, weight and height will be analyzed by using a t-test. Potentially dropouts after the first measurement will be analysed with respect to the social demographic data and compared to those of the patients who stay in the study. All dropout analysis will be done by means of an unpaired t-test.

All statistical analyses are done using Stata, version 11.

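### The dropout comparison has two incompatible test rules and leaves out the baseline CMD-SQ and patient-reported scores, so it cannot show selective loss on the exposure under study

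*Protocol article*

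**What the plan says.** All the rules for the dropout comparison stand in one paragraph of the Statistical analysis section of the protocol article.

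- Categorical variables: "the categorical variables as gender, citizenship, civil status, Charlson Index and educational level will be analyzed using a chi^2 test".
- Continuous variables: "For the continuous variables age, weight and height will be analyzed by using a t-test".
- Patients lost later: "Potentially dropouts after the first measurement will be analysed with respect to the social demographic data", in comparison with those who stay.
- Closing rule: "All dropout analysis will be done by means of an unpaired t-test".
- Missing answers: "Missing data will be labelled as missing in all the questionnaires".

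The Design section sets out what is collected before operation. For hip patients, "they are asked to fill in the questionnaires: CMD-SQ, EQ–5D, SF–12, RCS and OHS". For shoulder patients, "The shoulder patients are asked to fill in the questionnaires: CMD-SQ, EQ-5D, SF-12 and OSS". The Discussion acknowledges that dropout could threaten the study, plans 250 patients so that 202 remain, and expects a response rate near 90%.

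**The concern.** There are two faults, and the second carries more weight.

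First, one paragraph prescribes two tests for the same variables. An analyst who follows the closing sentence would run a t-test on citizenship, civil status and education.

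Second, the comparison list omits the variables that matter most here. The hypothesis is that anxious and concerned patients are less satisfied and have a poorer outcome, so baseline CMD-SQ is the exposure and the baseline patient-reported scores are natural predictors of the later ones. A patient lost after the first measurement should already have supplied them. If anxious patients who do badly return fewer forms, the estimated association shrinks, and a table of age, sex, education and similar items need not show any sign of it. The Discussion would use a positive result to recommend screening all hip and shoulder patients, so readers will want to know whether patients with high CMD-SQ scores stayed in the study.

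**Working it through.** **1. The two test rules side by side**

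| Variable | Earlier sentences | Closing sentence |
|---|---|---|
| Gender, citizenship, civil status, education, Charlson Index | chi-square | unpaired t-test |
| Age, weight, height | t-test | unpaired t-test |

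The rules agree only in the second row. Limiting the closing sentence to patients lost after the first measurement does not remove the conflict. Those patients are compared on the socio-demographic data, which by the article's own list include gender, citizenship, civil status and education.

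For a two-level variable the choice hardly matters. With an illustrative 30 of 48 dropouts against 95 of 202 completers, both tests give p = 0.054. For unordered categories it does matter, because a t-test compares means of arbitrary codes. Suppose one group is half in category 1 and half in category 3, and the other is wholly in category 2. The means are (1 + 3)/2 = 2 and 2, so there is no difference. Swap the labels 2 and 3 and the means become (1 + 2)/2 = 1.5 and 3. Same data, opposite answer.

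**2. Variables available and variables compared**

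Collected before operation in both groups: CMD-SQ, EQ-5D, SF-12 and OHS or OSS. Named in the dropout comparison: gender, citizenship, civil status, education, Charlson Index, age, weight and height. No variable is on both lists.

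**3. Number of dropouts the plan implies**

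From the Discussion, the implied loss is 1 − 202/250 = 19.2%, or 48 of 250. At a 90% response it is 25 of 250. The 202 itself cannot be recomputed, because the article gives no alpha, power, effect size or standard deviation for it.

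**4. When selective loss biases the result**

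This is a simulation of 1,000,000 patients with an assumed standardised slope of 0.30 of outcome on baseline CMD-SQ, logistic dropout, and a regression on those who remain. The slope and the dropout models are assumptions.

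| Loss depends on | Slope, 10% loss | Slope, 19.2% loss | Dropouts minus completers on CMD-SQ (SD), 10% / 19.2% |
|---|---|---|---|
| nothing | 0.30 | 0.30 | 0 / 0 |
| CMD-SQ only | 0.30 | 0.30 | 0.90 / 0.87 |
| outcome only | 0.28 | 0.27 | 0.27 / 0.26 |
| both, additively | 0.26 | 0.24 | 0.80 / 0.76 |
| both high together | 0.20 | 0.16 | 0.92 / 0.66 |

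The effect runs from none to 1 − 0.164/0.30 = 45% attenuation. With loss on CMD-SQ alone the slope is intact, although the plain correlation slips to 0.29 and 0.285.

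**5. A second scenario that keeps the planned response rate**

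Take a true r of 0.20. Patients in the worst quarter on both anxiety and outcome (8.4% of all at this r) are lost with probability 0.30 or 0.50, the others with probability 0.07.

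- Response = 1 − (0.084 × 0.30 + 0.916 × 0.07) = 91%, or 1 − (0.084 × 0.50 + 0.916 × 0.07) = 89%. Both are near the article's 90%.
- Observed r = 0.17 and 0.14.
- Dropouts differ from completers on baseline CMD-SQ by about 0.3 and 0.5 SD.

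**6. Could the omitted check detect this?**

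Power ≈ Φ(δ/√(1/n₁ + 1/n₂) − 1.96), with two-sided 0.05 assumed.

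- 48 against 202: √(1/48 + 1/202) = 0.161. Power is 46% for 0.3 SD and 88% for 0.5 SD.
- 25 against 225: √(1/25 + 1/225) = 0.211. Power is 30% for 0.3 SD and 66% for 0.5 SD.

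The check is feasible and would usually show a large imbalance. In one group of 250 it can miss a small one, so the size of the difference tells more than the p-value.

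**The case against.** The strongest reply is that the conflict is editorial. The closing sentence may only mean that the t-tests are unpaired, the dropout table is descriptive, and no estimate depends on it. That is fair as to weight. The sentence still says all, and the repair is one line.

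A second reply is that non-response is actively managed, with a second mailing and then a telephone call asking for the form or the reason for refusal. This reduces loss, but it does not measure whether those lost were more anxious.

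Three stronger readings are tempting, and the article does not support them.

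- A reader might infer that losing anxious patients biases the result in itself. Step 4 shows that it does not bias the slope; non-return must also depend on outcome.
- A reader might infer a complete-case analysis in which one blank CMD-SQ answer voids the score and numbers fall below 202. The article states only how missing answers are coded, and an analysis plan that is not shown may say more. It also describes six separately validated subscales and a scoring manual, not one 38-item total. The Sample size section gives 202 for shoulder patients and 36 for hip patients.
- A reader might infer that multiple imputation would repair the damage. Imputing from baseline data assumes that, given those data, loss does not depend on the unseen outcome. In the step 5 scenario with 50% loss it moved the slope only from about 0.14 to 0.145–0.152 (assumed correlations: CMD-SQ with baseline score 0.3, baseline score with outcome 0.3 to 0.5).

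**Conclusion.** The point holds on what the article itself fixes. The two test rules contradict each other, and the general one is invalid for unordered multi-category variables. The comparison list omits the exposure and the baseline patient-reported scores, which are collected in both groups, so the planned check cannot show directly whether loss is selective on them.

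This is a blind spot and not a demonstrated bias. If loss also depends on outcome, the association is understated: from 0.20 to about 0.17–0.14 under the assumed joint mechanism, and between 0 and 45% across the mechanisms in step 4. The loss probabilities, the true associations and the dropout models are all assumptions; the article supplies only the 250, the 202 and the response rate near 90%. An imbalance on CMD-SQ would be a warning and would not prove that the slope is biased. The test conflict alone is minor in practice. The variable list is the better reason to amend the text.

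**What to change.** In the Statistical analysis section:

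1. Delete the sentence assigning the unpaired t-test to all dropout analysis, or restrict it to continuous variables. Keep chi-square for the categorical variables and the unpaired t-test for the continuous ones.
2. Add the baseline CMD-SQ subscales, OHS or OSS, SF-12 and EQ-5D to the comparison of dropouts and respondents, at 12 and at 52 weeks.
3. Report each difference on these scores with its confidence interval, since 25 to 48 dropouts in a group of 250 give limited power for small differences.

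The cost is one edited sentence and a few more rows in a table. All the data are already collected before operation, and neither the sample size nor the visit schedule changes.

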## Discussion

The use of preoperative evaluation of patient anxiety and concern has not been done routinely in shoulder and hip surgery. This study aims to investigate the correlation between patient anxiety and concern and postoperative outcome. The hypothesis is that anxious and concerned patients are less satisfied with their treatment and have a poorer overall outcome of their treatment. If it is possible to confirm this hypothesis, it will be recommended to screen all hip- and shoulder-patients for anxiety and concern preoperatively. This will make it possible to optimize patient information, and to select patients with the likelihood of having a good patient reported outcome postoperatively.

The study is dependent on the fact that all patients fill in the questionnaire four times, and for that reason the study can be challenged by dropouts. Therefore, in order to get 202 patients (i.e. the required sample size) it is planned to include 250 patients. Experiences from other studies using the same versions of the PRO questionnaires have shown close to a 90 percent response rate which makes our patient number sufficient as planned in the power calculation
[6,43].

It is decided to send the questionnaire to the patients 12 and 52 weeks after the operation as it has been shown that these periods constitutes stable periods for patients functional ability and pain in their recovery after the operation
[44-47]. It is important to measure the patients when they are in a stable period because otherwise the outcome will be biased.

We have included the test-retest reliability of the CMD-SQ as this is recommended for each screening of a new population in a new context. The outcome of a reliability test, in this case a questionnaire, is a result of the data from this specific measurement in this specific patient group and not a result of the questionnaire itself
[42]. Therefore the result of the reliability test of CMD-SQ in this study can be compared to the results of other reliability tests of CMD-SQ, but it can not be used directly in a different population.

After having tested the hypothesis, the next step is to investigate the opportunity to help the patients identified as anxious and concerned preoperatively, - i.e. a high score on CMD-SQ. If this study detects a relationship between patients´ anxiety and concern, their self-reported outcome of treatment and their perceived quality of progress, it will be relevant to develop a method for helping these patients before surgery.

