**Discussion:**

If a correlation between patient anxiety and concern, patients´ perceived quality of treatment and patient reported outcome is found, it will be recommended to screen all hip- and shoulder-patients for anxiety and concern preoperatively. Besides, it would be relevant to carry out investigations of possible interventions towards anxious and concerned patients.

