The Danish questionnaire HVOK includes 46 items and deals with patients' priorities and satisfaction with treatment and is included in a revised form. The questionnaire has been pilot tested at 38 patients
[25]. Ten of the highest prioritised items were selected for this study. The patients respond on at five point Likert scale.

The Royal College of Surgeons of England has developed the "Questionnaire for patients who have had hip surgery" (RCS). The aim was to investigate patients´ satisfaction with surgery
[26]. It is relevant to include three items as supplementary questions in this study. The patients respond on at a five point Likert scale. This three items are 1) “In general, would you say your health is?”, 2) “How will you describe the result of your operation?” and 3) “Overall, how are the problems now in the hip on which you had surgery, compared to before your operation?”

Patient reported outcome (PRO) is defined as the patients outcome of the treatment measured by SF-12 (Short Form 12) and OHS (Oxford Hip Score) or OSS (Oxford Shoulder Score)
[27].

The UK questionnaires OHS and OSS are similar, but related to two different categories of patients, namely THA (Total Hip Arthoplasty) and shoulder-operated patients. The questionnaires are compiled and validated in Oxford University Hospital. Each questionnaire contains 12 items and both scores have been translated into Danish
[28]. The OSS has been translated into Danish and validated
[29]. The patients respond on at five point Likert scale and the sum scores can be between 12 and 60 points. 12 points reflects the best possible outcome, and a score above 36 is categorized as an expression of a poor patient-assessed outcome
[27].

SF-12 is an internationally and nationally validated questionnaire that evaluates patients' self-reported health perception. SF-12 is an abbreviated version of SF-36 and it contains 12 items, which are divided into physical and mental items. The patients respond on a Likert scale
[30-32].

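### Finding a correlation is made sufficient for recommending that all patients be screened and selected, with no minimum strength or predictive accuracy attached

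*Protocol article*

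**What the plan says.** The recommendation appears twice. In the abstract's Discussion paragraph the trigger is that a correlation of anxiety and concern with perceived quality and "patient reported outcome is found, it will be recommended to screen all hip- and shoulder-patients for anxiety and concern preoperatively". In the main Discussion the trigger is confirmation of the hypothesis, in which case "it will be recommended to screen all hip- and shoulder-patients for anxiety and concern preoperatively". The main Discussion then gives two uses for the screen: better patient information, and being able "to select patients with the likelihood of having a good patient reported outcome postoperatively".

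The hypothesis is that "anxious and concerned patients are less satisfied with their treatment and have a poorer overall outcome of their treatment".

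Under Statistical analysis, the evidence is multiple linear regression, one model from baseline to 12 weeks and one from baseline to 52 weeks. The main result is described as a correlation between CMD-SQ and the secondary outcomes (SF-12, EQ-5D, OHS/OSS, RCS and HVOK). The section adds "The analysis will be done separately and without mutual influence", without defining what is kept separate.

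The article also holds the ingredients for an accuracy analysis. Under Conceptual clarifications it gives CMD-SQ cut points, and for the Oxford scores it states that "a score above 36 is categorized as an expression of a poor patient-assessed outcome".

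**The concern.** Association and individual prediction are different claims. A regression coefficient can differ clearly from zero while the predictor hardly separates patients who will do well from those who will do badly. The plan passes from association to prediction with no condition in between. Any correlation judged to be present, however weak, meets the stated trigger.

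At stake is the main practical conclusion of the study: a recommendation to put every hip and shoulder patient through a mental-health questionnaire, and to use it to pick out likely good responders. If the observed correlation is small, following the plan as written would produce that recommendation without evidence that the questionnaire can do the job.

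**Working it through.** **Inputs from the article.** 250 THA and 250 shoulder patients (Sample size). A response rate close to 90% (Discussion). A required number of 202 (Sample size, Discussion).

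**Assumptions.** Two-sided alpha of 0.05, since the article states none. Poor outcome in 10% to 25% of patients, since no prevalence of OHS/OSS above 36 is given. Bivariate normal score and outcome, in line with the article's own normality assumption. Screen-positive means the highest 20% of CMD-SQ scores.

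**Step 1: responders.** 250 × 0.90 = 225 per group, and 2 × 225 = 450 pooled. 225 exceeds 202, so the article's allowance for dropout holds. The 202 itself cannot be rebuilt, because alpha, power, effect and SD are not given. It is tied to improvement in EQ-5D, not to a correlation.

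**Step 2: smallest significant correlation.** r = t / √(t² + n − 2).
- n = 225: t = 1.971, so r = 1.971 / √(3.884 + 223) = 0.131 and r² = 0.017.
- n = 450: t = 1.965, so r = 1.965 / √(3.862 + 448) = 0.092 and r² = 0.009.

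**Step 3: what that correlation predicts.** Let X be the score and Y the outcome, with correlation r. A poor outcome is Y above c (c = 1.282 for 10%, 0.674 for 25%), and a flagged patient has X above 0.842. Then P(poor | X = x) = 1 − Φ((c − r·x) / √(1 − r²)). Integrating over x gives:

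| r | Poor outcome (assumed) | AUC | Poor outcomes found among the flagged 20% | Risk if flagged | Risk if not flagged |
|---|---|---|---|---|---|
| 0.131 | 10% | 0.57 | 27% | 13.4% | 9.1% |
| 0.131 | 25% | 0.56 | 25% | 31.0% | 23.5% |
| 0.092 | 10% | 0.55 | 25% | 12.4% | 9.4% |
| 0.092 | 25% | 0.54 | 23% | 29.2% | 23.9% |

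Flagging 20% of patients at random would find 20% of poor outcomes, and an uninformative score has an AUC of 0.50.

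**Step 4: would a stricter alpha cure this?** As an illustration, take 0.05 / 10 = 0.005. The smallest significant r becomes 0.187 (r² = 0.035) at n = 225 and 0.132 (r² = 0.017) at n = 450. A correlation explaining 2–3% of variance would still meet the trigger, so the gap lies in the missing accuracy criterion and not in the significance level.

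**The case against.** **The figures are a boundary case.** Every significance test has a smallest significant effect, and 0.131 says nothing about what this study will observe. That is correct. The calculation shows only what the trigger would let through. A much stronger correlation could be useful for prediction, but the stated rule does not distinguish the two.

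**The recommendation is partly about something else.** It is to screen for anxiety and concern. The article reports that CMD-SQ was validated against an interview standard (701 patients, kappa 0.86), and the first benefit named is better patient information. Intervention is presented as later work. This stands in part: only the clause on selecting likely good responders clearly requires prediction of individual outcome. Even so, the case for screening everyone rests on the link with outcome, and no strength is required of that link.

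**A stronger reading is tempting but not supported.** With five instruments and two time points, a reader might infer that one positive result among many unadjusted tests is enough. If so, the chance of at least one false positive would be 1 − 0.95^10 = 40%, or 1 − 0.95^20 = 64% if split by joint, for independent tests. The article does not say that one positive analysis suffices. Its hypothesis is a conjunction: less satisfied and poorer outcome. If at least one of four HVOK/RCS tests and at least one of six SF-12, EQ-5D or OHS/OSS tests must be positive, independent tests give (1 − 0.95^4) × (1 − 0.95^6) = 0.186 × 0.265 = 4.9%. The rate therefore depends on the reading. Alpha and multiplicity handling may also sit in an analysis plan that is not shown, so their absence here is no finding.

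**Naming a single primary test would not help.** Letting 52-week OHS/OSS alone decide would drop perceived quality, which is half of the hypothesis, and would leave the 0.131 threshold in place.

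**Conclusion.** The point holds in limited form. The abstract and the Discussion make the presence of a correlation, or a confirmed hypothesis, sufficient for recommending universal screening and for selecting likely good responders. The analysis described provides only regression and correlation, and no minimum strength or predictive accuracy is tied to the recommendation.

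The weakest result that meets the trigger explains 1.7% of variance in one group of 225, or 0.9% in 450 pooled. For one group it means an AUC only 0.06–0.07 above chance and 5–7 percentage points more poor outcomes found than by flagging at random. That would barely support selecting individuals.

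These sizes rest on an assumed two-sided 0.05, an assumed poor-outcome prevalence of 10–25%, bivariate normality and a 20% flag rate. The mismatch between evidence and conclusion does not depend on them. The finding does not say that the study has a high false-positive rate, or that the true correlation is small.

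**What to change.** 1. Reword the abstract's Discussion paragraph and the main Discussion so that a correlation supports only the statement that preoperative anxiety and concern are associated with perceived quality and outcome.
2. Make any statement about screening or selection depend on estimates, with 95% confidence intervals, of the sensitivity, specificity, positive predictive value and AUC of preoperative CMD-SQ for an OHS/OSS above 36 at 52 weeks.
3. Report also the gain in AUC when CMD-SQ is added to age, sex, Charlson Index and baseline OHS/OSS, with its 95% confidence interval. These are already collected, and a screen is worth having only if it adds to them.

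**Cost.** No new data, a modest amount of extra analysis and a more modest conclusion. The AUC will be imprecise if few patients exceed 36. By the Hanley–McNeil formula, SE = √{[A(1 − A) + (m − 1)(a − A²) + (k − 1)(b − A²)] / (m·k)}, with a = A/(2 − A), b = 2A²/(1 + A), m poor outcomes and k others. For A = 0.57, 22 poor outcomes among 225 (about 10%) give √(19.8 / 4,466) = 0.067, a 95% interval of about ±0.13. With 56 (about 25%) the SE is 0.045, or about ±0.09. Such an interval would still show how little, or how much, the data can say about selection.
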